# Comparing Online and On-Site Cognitive Behavior Therapy in Major Depressive Disorder: Protocol for a Noninferiority Randomized Controlled Trial

**DOI:** 10.2196/29726

**Published:** 2022-04-08

**Keywords:** online intervention, randomized controlled trial, major depressive disorder

## Abstract

**Background:**

The incidence of mental health disorders in Canada is increasing with costs of CAD $51 billion (US $40 billion) per year. Depression is the most prevalent cause of disability while cognitive behavioral therapy (CBT) is the best validated behavioral depression treatment. CBT, when combined with mindfulness meditation (CBT-M), has strong evidence for increased efficacy. While randomized controlled trials (RCTs) have demonstrated online CBT-M efficacy, comparisons with in-office delivery are lacking.

**Objective:**

The aim of this research is to assess whether online group CBT-M (with standard psychiatric care) is non-inferior in efficacy and more cost-effective than office-based, on-site group CBT-M at post-intervention and 6-months follow-up in major depressive disorder. The study will also assess whether digitally recorded data (ie, online workbooks completed, Fitbit step count, and online text messages) predict depression symptom reduction in online participants.

**Methods:**

This single-center, two-arm, noninferiority RCT employs assessor-blinded and self-report outcomes and economic evaluation. The research site is the Centre for Addiction and Mental Health (Toronto), a research-based psychiatry institution where participants will be identified from service wait lists and through contacts with other Toronto clinics. Inclusion criteria are as follows: (1) aged 18-60 years, any ethnicity; (2) Beck Depression Inventory-II (BDI-II) of mild severity (score ≥14) with no upper severity limit; (3) Mini-International Neuropsychiatric Interview-confirmed, psychiatric major depressive disorder diagnosis; (4) fluent in English. All patients are diagnosed by staff psychiatrists. Exclusion criteria are as follows: (1) receipt of weekly structured psychotherapy; (2) observation of Diagnostic and Statistical Manual of Mental Disorders (5th Edition) criteria for severe alcohol or substance use disorder (in past 3 months), borderline personality disorder, schizophrenia (or other primary psychotic disorder), bipolar disorder, or obsessive-compulsive disorder; (3) clinically significant suicidal ideation (imminent intent or attempted suicide in the past 6 months); and (4) treatment-resistant depression. All participants receive standard psychiatric care, experimental participants receive online group CBT-M, and controls receive standard care in-office group CBT-M. The online group program (in collaboration with NexJ Health, Inc) combines smartphone and computer-accessed workbooks with mental health phone counselling (16 hours in 16 weeks) that coordinates software interactions (eg, secure text messaging and Fitbit-tracked walking). The primary outcome is BDI-II, and secondary outcomes are anxiety (Beck Anxiety Inventory), depression (ie, Quick Inventory of Depressive Symptomatology and 17-item Hamilton Depression Rating Scale), mindfulness (Five-Facet Mindfulness Questionnaire), quality of life (European Quality of Life Five Dimension), and pain (Brief Pain Inventory).

**Results:**

Based on prior studies with the BDI-II and 80% power to reject an inferiority hypothesis with a 1-sided type I error rate of 5%, a sample of 78 per group is adequate to detect small-to-medium–effect sizes.

**Conclusions:**

This study assesses online CBT-M efficacy and noninferiority in relation to in-person CBT, and the cost-effectiveness of both interventions.

**Trial Registration:**

ClinicalTrials.gov NCT04825535; https://www.clinicaltrials.gov/ct2/show/NCT04825535

**International Registered Report Identifier (IRRID):**

DERR1-10.2196/29726

## Introduction

Mental health disorders are Canada’s most costly chronic health problem for both health systems and patients, and they are increasing in incidence. The current economic costs of mental health are estimated at CAD $51 billion annually (US $40 billion), with CAD $42.3 billion (US $33 billion) in direct costs to the Canadian health care system [1]. Depression is a commonly diagnosed mental health disorder, representing the most prevalent cause of disability worldwide [2]. Cognitive behavioral therapy (CBT) is the best validated psychotherapy for the treatment of depression, with decades of research demonstrating its efficacy [3]. Despite demonstrated efficacy, many individuals are not able to access adequate CBT treatment due to the limitations of face-to-face delivery. Improving access to CBT services is crucial to overcoming the treatment barriers (including geographic distance, cost, time, and perceived stigma) that currently prevent access to necessary mental health care for individuals with depression [4-6]. Recent research projects have focused on internet-based CBT (with internet-delivered or telephone-based interventions) as a means of delivering cost-effective treatment to populations that are unable to access high-quality psychotherapy services within traditional in-office environments. The structured and goal-directed modules of CBT are well suited to online delivery, and numerous randomized controlled trials (RCTs) have indicated that internet-delivered CBT is highly effective in symptom reduction and depression remission [7-9]. In recent years, CBT has been integrated with mindfulness meditation (CBT-M) following strong evidence for the increased efficacy when CBT and mindfulness meditation are combined [10]. While other trials support online CBT and mindfulness efficacy versus control groups [11-18], no prior trial, to our knowledge, has compared the efficacy and cost-effectiveness of online group CBT-M versus standard office-based group CBT-M.

Previous noninferiority RCTs have indicated that guided online CBT can be at least as effective as in-person CBT for the treatment of depression; however, these studies are limited by the use of small, nonclinical samples and do not include cost-effectiveness comparisons [19-21]. Research is now required with an adequate sample size and in-depth cost comparisons to fully establish noninferiority and cost-effectiveness [22]. This study has been registered with ClinicalTrial.gov (NCT04825535).

## Methods

### Aim

This study has the 3 following aims: (1) to evaluate whether online group CBT-M (with standard psychiatric care) is noninferior in efficacy compared with office-based group CBT-M (with standard care) as measured by the BDI-II (Beck Depression Inventory-II) score in the treatment of adults with major depressive disorder (MDD) [23]; (2) to evaluate whether online group CBT-M is more cost-effective than office-based group CBT-M post intervention and at 6 months post-intervention follow-up; (3) to assess, within the online group CBT-M intervention group, whether digitally recorded adherence data (ie, online workbooks completed, Fitbit tracked steps, online text messages exchanged, and phone sessions completed) predict outcome benefits as indicated by the changed BDI-II score [23].

### Ethical Considerations, Recruitment, and Randomization

The study has been approved by the Research and Ethics Board at the Centre for Addiction and Mental Health (CAMH) (reference 087/2020). The participants will be identified from the wait lists within the CAMH General Adult Psychiatry and Health Systems Division, which annually services thousands of MDD patients. The attending physician or clinician identifies prospective participants and asks for their verbal consent to receive more information about the research. Once the patient’s attending physician or clinician obtains verbal consent for more information about the research project, he or she can refer eligible participants to the research analyst who explores interest with the participant, and after an expressed interest, reviews and explains the study. Eligibility screening and written consent are undertaken in person prior to randomization. The study biostatistician performs electronic randomization with study IDs blindly assigned to intervention (online CBT-M plus standard psychiatric care) and control (office-based group CBT-M plus standard psychiatric care) groups. The study ID information with the respective group allocation will be transferred onto cards placed in opaque, individual, sealed envelopes. After a participant completes baseline questionnaires, the research analyst opens the next envelope in sequence to determine group allocation and study ID. Based on the results of previously successful RCTs, including the one conducted at the identical study site, we will recruit 100 participants per group or 200 overall (N=200). One-sided type 1 error rate is set at 5%. We chose a margin of 3 and a correlation of 0.70, indicating a sample size of 78 per group in 2 groups, which is more than adequate for the detection of small-to-medium effect sizes. The 16-week intervention entails 16 weekly group CBT in-person sessions (control group) (1.5 hours in duration) and 16 weekly, phone-based navigator-health coach sessions (16 hours in duration per subject in group or individual formats). Participants are assigned to review 1-2 workbooks and related videos per week (16-32 workbooks per 16 weeks). Assessments take place at post-intervention and 6 months follow-up. Given the recruitment, consent, and intervention target of 48 participants per year, we expect to complete the study within 2.5 to 3 years.

#### Inclusion Criteria

The inclusion criteria are as follows: (1) individuals 18-60 years of age; (2) BDI-II of at least mild severity (score ≥14) with no upper severity limit [23]; (3) MINI (Mini-International Neuropsychiatric Interview)-confirmed diagnosis of MDD [24]; and (4) fluency in English. All participants are diagnosed by a CAMH staff psychiatrist with diagnosis confirmed via the MINI [24], administered at the screening visit.

#### Exclusion Criteria

The exclusion criteria are as follows: (1) individuals currently receiving weekly structured psychotherapy; (2) individuals who meet DSM-V (Diagnostic and Statistical Manual of Mental Disorders, 5th Edition) criteria for severe alcohol or substance use disorder (in the past 3 months), borderline personality disorder, schizophrenia, or any other primary psychotic disorder, bipolar disorder, or obsessive-compulsive disorder; (3) individuals who manifest clinically significant suicidal ideation defined as imminent intent or attempted suicide (in the past 6 months); and (4) individuals who are judged to have treatment-resistant depression, as defined by failure in at least 2 trials of antidepressant medications or a course of psychotherapy during the current depressive episode [25].

### Interventions

#### Online Intervention

The online group CBT-M program combines online-accessed workbooks with phone-based navigator coaching that assists with the coordination and support of multiple software interactions (eg, secure text messaging, Fitbit tracked walking, and food monitoring via photography). Each participant is loaned a Fitbit HR Charge 4 (Fitbit Inc), which assesses physical steps and 24-hour heart rate, averaged in 5-second intervals. Intervention content builds on 6 online RCTs with students [26-32], 1 RCT with adults with type 2 diabetes [11,33,34] (where significant mental health and blood glucose benefits resulted), and 1 online RCT with youth diagnosed with MDD [22]. The content contains 24 workbook chapters on multiple topics derived from the focus group study (eg, Living By Your Truths, Overcoming Wired-ness and Tired-ness, Mindfulness and Relationships, Loss and Grief, Resilience, Befriending Ourselves, Befriending Your Body with Exercise, Body Image, Intimacy, Forgiveness, Overcoming Procrastination, Dealing with Negative Moods, Stress Resilience, Reducing Performance Anxiety, and Cultivating Inspiration), addressed in sequences mutually agreed on by the participants and navigator-coaches.

The online CBT-M groups address structured tasks that elevate mood and decrease anxiety. Depressive social withdrawals are identified and reflected on while corrective emotional experiences are elicited, structured, and supported. Healthy internet interactions are reinforced by the web-based program content (24 workbooks and 56 videos), with priorities guided by participant interests. While internet-based contacts are sometimes distracting “escapes” (eg, Netflix movies and video game playing), they can be productive, socially engaging events (eg, TED Talks, CBT discussion, and mindfulness instructions) where role-modeling coordinates with learning. Group members stimulate and reinforce health behavior adoptions (exercise, CBT, mindfulness, sleep hygiene, diet, and text message encouragement) and transformations from distractive media fixations to positive learning and enjoyment. Internet-based contacts integrate with face-to-face professional and familial contacts and social intimacy development. Group online CBT-M tasks emphasize applying CBT-M methods in accord with content themes, which are decatastrophizing, overcoming perfectionism, sound sleep, self-befriending, courage development, forgiveness, interpersonal mindfulness, and autonomous generosity. This progression coordinates physical and cognitive changes that integrate interpersonal contacts with self-management. The tracking of walking exercise and heart rate (HR), on a 24-hour basis, captures HR elevations that reflect episodes of anxiety and negative affect (elevated HR with minimal movement). There is selective sharing of Fitbit bio-behavioral data with designated staff and group members. Reduced HR often accompanies mindfulness practice while mildly elevated HR is closely associated with walking (ie, movement-affected HR). Self-modification goals involve improving autonomic nervous system balance through appropriate exercise, improved sleep hygiene, and restorative sleep [35].

#### Office-Based Intervention

The on-site, usual-care CBT group follows the structure of the “Mind Over Mood” workbook in reviewing CBT concepts and procedures [36]. A series of worksheets assist participants in differentiating moods from thoughts and situational influences, leading to modifications of thinking, behavior, emotion, and mood.

Difficulties with cognitive change are assumed to be associated with self-acceptance deficits and negative mood dominance. Increased self-acceptance is linked with mindfulness experiences, which involve “more focusing on the present moment” and on nonjudgmental acceptance of ongoing experience. Mindful breathing awareness is described in content on “balanced deep breathing” and in tension releases achieved via progressive muscle relaxation practice [37].

An emphasized structure is the automatic thought record by which negative, disturbing thoughts are identified, and attention directed to alternate thoughts evaluated as clearer and less distorted. These transitions are more difficult when immersions in negative moods diminish the confidence in finding a “better” thought. Accordingly, self-efficacy is an important goal, emphasized in exchanges of support between group members and in enhanced experiences of self-acceptance.

Behavioral activations are structured for the development of increased awareness and observations of how self-control resources elicit gratifying activities. On the basis of behavioral activation practices, cognitive restructuring strategies utilize the automatic thought record or experiential approximations of the automatic thought record [38].

Another major component of group CBT-M at CAMH involves examinations of core beliefs where multiple techniques are employed (eg, self-observation logs and historical self-reviews) in the group setting and in individual homework assignments between sessions [38].

### Hypothesis

Online group CBT-M will be noninferior to standard, office-based group CBT in the treatment of MDD (as indicated by BDI-II score change) when online and office-based treatment groups are compared, using both intention-to-treat and per-protocol analyses. Online group CBT-M will be more cost-effective than standard, office-based group CBT, as measured by cumulative costs and quality-adjusted life years (QALY) calculated in the cost utility analysis. Within the online CBT-M intervention participant group, digitally recorded adherence data will predict outcome benefits (as reflected in the BDI-II score change). Adherence over time will be compared within each participant using a generalized estimating equation logistic regression model with an autoregressive 1 (AR1) correlation structure.

### Outcome Measures

#### Primary Outcome

The primary outcome measure is the BDI-II [23]. It is a 21-item self-report scale, measuring symptoms of depression with a 4-point Likert scale (0 to 3), with higher scores indicating more severe depressive symptoms. The customary cut-off scores for mild depression are 14 to 25, moderate depression 26 to 30, and severe depression 31 and greater.

#### Secondary Outcomes

The secondary outcomes assess the following: anxiety (Beck Anxiety Inventory) [39]; depression (QIDS [Quick Inventory of Depressive Symptomatology] [40] and HDRS-17 [17-item Hamilton Depression Rating Scale], consisting of an interview with a blinded-assessor rater) [41]; mindfulness (FFMQ [Five-Facet Mindfulness Questionnaire]) [42]; quality of life (EQ-5D [European Quality of Life Five Dimension]) [43,44]; patient costs (health care cost diary for major depression) [45]; and pain (brief pain inventory) [46].

All self-report measures and the HDRS-17 interview are carried out at the same CAMH mood and anxiety research clinic in identical assessment rooms. The HDRS-17 interviewer-assessor is blinded to intervention and control conditions for the trial duration and is experienced in the blinded-assessor role with similar conditions conducted at the identical study site used in this trial [22].


#### Secondary Outcomes

A similar modeling approach will be used for each secondary outcome (Beck Anxiety Inventory, QIDS, and HDRS-24), mindfulness (FFMQ [Five-Facet Mindfulness Questionnaire]), pain (brief pain inventory), health care cost diary for major depression, and quality of life (EQ-5D). While noninferiority margins per outcome are nonexistent, we will present probabilities for a range of margins based on fractions of the minimally clinical important difference for these scales (where available) or fractions of a standard deviation. All primary and secondary outcomes will be analyzed as continuous variables, with outcomes modelled as normal, *t*, rescaled beta, log-normal, or gamma distributions, whichever is most appropriate.

#### Postintervention Period Outcomes

We will examine BDI-II changes over time across the 2 intervention delivery models during a 6-month post-intervention period. To give a quantitative overview of changes between and within groups over 6 months, all study outcomes will be assessed using linear mixed effects models incorporating within-person correlation. Mixed effects models allow for including partial data (eg, from participants with missed visits or who dropped out prematurely) while accounting for repeated within-person data [47]. The baseline and follow-up scores (up to 10 months from baseline) will form the dependent variable and intervention group, time, and the time-treatment interactions will be the independent variables. Within-person correlation of residuals will be handled by an AR1 error structure. Through the examination of estimated model parameters and their 95% confidence intervals, we can assess whether changes over time are similar between groups and whether differences between groups at any given time are clinically important.

### Adherence

Multiple analyses are used to assess adherence in the online group CBT-M program and the relationship of adherence to both time and potential predictors. Adherence is cumulatively and quantitatively defined as a binary variable (adherent or nonadherent). We will assess adherence over 2 distinct periods—0 to 2 months and 2 to 4 months—so each participant has up to 2 adherence measures. Our first analysis of adherence will simply be the calculation of percentages adhering in each of the time windows. The chi-squared or Fisher exact tests will compare adherence within each of the time windows. All further analyses will be carried out on the sequence of 2 adherence measures on each participant using a generalized estimating equation logistic regression model with an AR1 correlation structure. A series of models will be run, which is as follows: to check adherence changes over time, we will use time as a categorical predictor variable and assess its importance using a Wald test; to examine predictors of adherence, variables (steps per day or HR, workbooks completed, text messages exchanged, videos watched, and phone counselling calls completed) measured at the start of each of the 2 time periods will be added as predictors for the corresponding adherence outcome. These time-varying predictors help us assess whether the most recent assessment of a given predictor predicts adherence over the following 2 months.

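### The adherence-predictor GEE uses an AR1 working correlation although month-2 predictors partly result from window-1 adherence, so it can miss its stated target

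*Protocol article*

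**What the plan says.** After simple percentages and chi-squared or Fisher tests, the Adherence section of the protocol article sends every further adherence analysis to one model type, fitted "using a generalized estimating equation logistic regression model with an AR1 correlation structure". Adherence is binary and is assessed for months 0 to 2 and months 2 to 4, so "each participant has up to 2 adherence measures".

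The first model in the series has time alone as predictor. The next models add "steps per day or HR, workbooks completed, text messages exchanged, videos watched, and phone counselling calls completed", each "measured at the start of each of the 2 time periods will be added as predictors for the corresponding adherence outcome". The purpose is stated: "These time-varying predictors help us assess whether the most recent assessment of a given predictor predicts adherence over the following 2 months".

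The Hypothesis section has a related sentence: "Adherence over time will be compared within each participant using a generalized estimating equation logistic regression model with an autoregressive 1 (AR1) correlation structure". It describes the comparison over time and names no time-varying predictor.

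The Aim section classes workbooks, steps, text messages and phone sessions as adherence data.

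**The concern.** The stated question concerns the mean of adherence in a window given the predictor value at the start of that window, E[Y_t | X_t]. A GEE with a non-diagonal working correlation estimates this consistently only under an extra condition: given X_t, the predictor values from the other window must carry no further information about Y_t.

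That condition is doubtful here. The month-2 count of workbooks, texts, videos or calls is built up during months 0 to 2, the same period that the first adherence measure covers. On the article's own classification most of these measures are adherence data. So X2 tells us about Y1 beyond what X1 does. The link is weaker for steps and heart rate, which exist before the program starts and are less clearly products of adherence.

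At stake is whether a useful early-warning measure is reported as weak or not predictive, in a single arm planned at 100 participants. Because the fault lies in the point estimate, a robust variance does not cure it.

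**Working it through.** **Inputs from the article.** Two adherence measures per participant; logistic GEE with AR1; predictors at the start of each window; 100 participants in the online arm (recruitment section); an example loss to follow-up of 10% online (Missing Data), hence 100 × 0.90 = 90. The article gives no figure for this analysis, so there is nothing to reproduce.

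**Inputs assumed.** Residual correlation ρ, strength of feedback and size of predictor effect. None is in the article, so each was varied.

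**Algebra.** With two measures, AR1 is the same as exchangeable: one parameter ρ. Write v_t = μ_t(1 − μ_t). One participant's contribution to the slope equation is

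1/(1 − ρ²) × { [X1 − ρ·X2·√(v2/v1)]·(Y1 − μ1) + [X2 − ρ·X1·√(v1/v2)]·(Y2 − μ2) }.

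The same-window terms X1(Y1 − μ1) and X2(Y2 − μ2) have mean zero at the target. The cross term −ρ·X2·√(v2/v1)·(Y1 − μ1) has mean zero only if ρ = 0 or X2 carries no information on Y1 beyond X1. Under independence ρ is set to 0 and the cross term is absent.

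*Illustration.* Suppose a workbook count starts at 0, averages 10 at month 2 in those adherent in window 1 and 4 in the others, and is divided by 4. The difference is (10 − 4)/4 = 1.5. With 70% adherent, Cov(X2, Y1) = 1.5 × 0.70 × 0.30 = 0.315. Taking the variance ratio as about 1 and ρ = 0.17, the cross term averages −0.17 × 0.315 = −0.054 per participant. It does not shrink with sample size, and it pulls a positive slope down.

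**Simulation 1, count predictor.** logit P(Y1) = 1 + s·u, with u a standard normal personal propensity; X2 as above with SD 2.5 before division; logit P(Y2) = a + 0.5·X2 + s·u; s = 0.7, 1.0, 1.5; time in the model; n = 400,000 for the large-sample values and n = 100 for coverage and power.

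| ρ | Log OR, independence | Log OR, AR1 | AR1 ÷ independence | 95% CI coverage, AR1 | Power, independence v AR1 |
|---|---|---|---|---|---|
| 0.09 | 0.61 | 0.44 | 0.72 | 75% | 75% v 52% |
| 0.17 | 0.71 | 0.39 | 0.55 | 60% | 86% v 47% |
| 0.30 | 0.87 | 0.31 | 0.36 | 31% | 96% v 41% |

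Coverage under independence was about 95% throughout. Repeats with other intercepts a moved the log odds ratios by no more than about 0.06.

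**Simulation 2, other assumptions.** X2 depends on Y1 and on propensity; time in the model.

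| Setting | Independence | AR1 | Ratio |
|---|---|---|---|
| Base case, ρ = 0.17 | 0.90 | 0.69 | 0.77 |
| Stronger dependence, ρ = 0.34 | 1.06 | 0.60 | 0.57 |
| Weaker heterogeneity, ρ = 0.06 | 0.62 | 0.57 | 0.91 |
| Steps-type, non-zero start value | 0.85 | 0.79 | 0.92 |
| X2 linked to Y1 only through shared propensity | 0.80 | 0.69 | 0.86 |
| X2 unrelated to Y1 and to propensity | 0.36 | 0.36 | 1.00 |
| Feedback, ρ = 0 | 0.49 | 0.49 | 1.00 |
| Negative residual correlation, ρ = −0.22 | 0.31 | 0.48 | 1.57 |
| Predictor effect opposite to feedback | −0.14 | −0.36 | 2.53 |

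In the base case at n = 90, coverage was about 95% under independence and 68% under AR1, while power was near 100% and 95%. For steps-type predictors the shortfall across all the assumptions tried was 3% to 26%.

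**Time in the model.** With the window indicator left out, independence returned only 0.02 to 0.18 for the count predictor of Simulation 1, against 0.61 to 0.87 with it. Most counts are presumably 0 at program start, so without the indicator the slope also absorbs the change in adherence between windows.

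**The case against.** The strongest objection is that the direction and size are not known. A reader might infer that AR1 always shrinks these effects toward zero. The article does not support that: it gives no residual correlation, feedback strength or predictor effect. The bias disappears if either ingredient is absent, and it reverses if residual correlation is negative or the predictor effect opposes the feedback. This stands, so the claim about direction must be conditional. Positive within-person correlation is nevertheless the usual reason for choosing AR1, and feedback is likely for the counts.

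A second objection is that the independence estimate is not a pure predictor effect. When the built-in effect in Simulation 1 was set to zero, independence still returned 0.14, 0.25 and 0.46 (s = 0.7, 1.0, 1.5), while AR1 returned about 0. Part of what AR1 removes is therefore stable personal propensity. A reader might infer that real, causal drivers of adherence are being lost; the documents do not support that reading. The stated purpose is prediction, though, and for prediction that association belongs in the estimate.

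Third, the loss of power is not general. It was large in Simulation 1 and small in the base case of Simulation 2.

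Finally, the consequence is limited. The third aim concerns prediction of BDI-II change, whereas this GEE predicts adherence. That is correct and restricts the weight of the point.

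None of this makes AR1 consistent for the stated target. Nor is the choice left to a later plan, because the article names AR1 for all these models.

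**Conclusion.** The point holds in conditional form. For models with time-varying predictors, the AR1 working correlation in the Adherence section is not consistent for the stated target when month-2 values carry information about window-1 adherence and residual correlation is non-zero. The first condition follows closely from the article's own description for workbooks, texts, videos and calls, and less strongly for steps and heart rate. The second is an assumption.

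With positive residual correlation and a predictor effect in the direction of the feedback, the AR1 log odds ratio is roughly 35% to 95% of its target, and interval coverage can fall well below 95%. Those figures rest wholly on assumed inputs and show a range, not a forecast for this trial.

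A reader might also infer that the Hypothesis sentence is wrong, or that the trial's main conclusions are at risk. Neither follows. That sentence describes change over time, for which AR1 is acceptable. The primary noninferiority analysis, the cost-utility analysis and the BDI-II prediction aim do not use this model. This is a correctable error in an ancillary, single-arm analysis.

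**What to change.** Change the Adherence section only. Keep AR1 for the time-only model. For every model with time-varying predictors, state that the time-window indicator is included and that an independence working correlation is used with participant-clustered robust standard errors. Describe the result as a predictive association that includes stable personal propensity, not as a causal effect.

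A logistic regression of window-2 adherence on month-2 values is an alternative. With time in the model it is equivalent to the independence GEE only for predictors that are constant at program start. It is not equivalent for steps or heart rate, which already vary between participants at that point.

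The cost is one line of text and one software option, plus a small loss of efficiency if the predictors were in truth exogenous.

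### Aim 3 asks whether online adherence predicts BDI-II change, but every adherence model described has adherence as its response, so the plan as written does not test the aim

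*Protocol article*

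**What the plan says.** Three places in the protocol article set the same question. The abstract's Objective asks whether the digital data "predict depression symptom reduction in online participants". The Aim section names the exposure as "digitally recorded adherence data (ie, online workbooks completed, Fitbit tracked steps, online text messages exchanged, and phone sessions completed", and asks whether these "predict outcome benefits as indicated by the changed BDI-II score". The Hypothesis section expects that, among online participants, "digitally recorded adherence data will predict outcome benefits (as reflected in the BDI-II score change". In all three, usage is the predictor and BDI-II change is the outcome.

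The analysis text points the other way. Immediately after that hypothesis, the Hypothesis section states: "Adherence over time will be compared within each participant using a generalized estimating equation logistic regression model". The Adherence section gives the detail. "Adherence is cumulatively and quantitatively defined as a binary variable (adherent or nonadherent", and it is assessed over two windows, "0 to 2 months and 2 to 4 months". After simple percentages and chi-squared or Fisher tests, all further analyses there use each participant's pair of binary adherence values as the response in a GEE logistic model with AR1 correlation. One model has time as the predictor. Others add "variables (steps per day or HR, workbooks completed, text messages exchanged, videos watched, and phone counselling calls completed) measured at the start" of each window, to see whether they predict adherence over the two months that follow.

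**The concern.** The question and the model have different response variables. A model of who adheres, and when, says nothing about whether those who use the programme more improve more on BDI-II. Aim 3 is one of three stated aims and appears in the abstract. If no BDI-II model is fixed for it, one will have to be chosen later, from several usage measures, two windows and more than one follow-up time. That leaves room for selective reporting.

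The predictor model also has a timing fault. Usage counts taken at the start of the first window precede any use of the programme, so they cannot distinguish one participant from another.

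**Working it through.** The article gives no sample size, effect size or power figure for aim 3, so there is no figure to reproduce. The check is to list each stated model and compare its response and predictors with the aim.

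| Section of the article | Response | Predictors | Usage or adherence term for BDI-II? |
|---|---|---|---|
| Aim and Hypothesis (the question) | BDI-II change, online arm | workbooks, steps, texts, phone sessions | required |
| Analyses, Primary Outcome: ANCOVA | BDI-II change, baseline to 16 weeks | baseline score, group | no |
| Same, covariate sensitivity analysis | BDI-II change | the above plus age and baseline anxiety, HDRS-17, pain and mindfulness | no |
| Postintervention Period Outcomes: mixed model | BDI-II over time | group, time, their interaction | no |
| Hypothesis: GEE logistic | binary adherence | time | BDI-II absent |
| Adherence: GEE logistic with time | binary adherence | time | BDI-II absent |
| Adherence: GEE logistic with predictors | binary adherence | steps or HR, workbooks, texts, videos, calls | BDI-II absent |

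In the Primary Outcome section adherence affects the BDI-II analyses only through who is counted in the per-protocol and intention-to-treat sets. It is never a term in a model. The number of stated models with BDI-II as response and usage or adherence as predictor is 0.

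**Overlap of predictors and response.** The Aim section calls four measures the adherence data: workbooks, steps, texts and phone sessions. All four reappear in the Adherence section as predictors of adherence. HR and videos are in the second list only.

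**Timing.** Write A(i,t) for participant i's binary adherence in window t (1 = months 0 to 2, 2 = months 2 to 4), and X(i,t) for a usage count at the start of that window. The pooled model, with time included, is

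logit P[A(i,t) = 1] = a + g·I(t = 2) + b·X(i,t).

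- At month 0, before any use, X(i,1) = 0 for every i, so window 1 reduces to logit P = a. It contains no contrast in X.
- At month 2, X(i,2) varies, so window 2 gives logit P = a + g + b·X(i,2).

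The coefficient b is therefore estimated from differences between people in window 2 only. Counting steps or HR as one item, this applies to 4 of the 5 listed predictors (workbooks, texts, videos, calls). With the planned 100 online participants there are 100 × 2 = 200 person-windows, of which 100 (half) hold no between-person information on those four.

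**The case against.** The strongest reply is that the Adherence section never claims to test aim 3. It announces its scope as adherence in relation to time and possible predictors, and its phrase about all further analyses can fairly be read as further analyses of adherence. On that reading the BDI-II model has merely been left out of a condensed article and may stand in a full protocol or SAP that is not shown. This has some force: the text does not show that the trial team cannot or will not run such a model. It does not remove the point, because the Hypothesis section does not leave the analysis of aim 3 open. It follows that hypothesis directly with a named model, and the named model has the wrong response.

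A reader might also infer several stronger things that the article does not support:

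- *That all predictors are measured before use begins.* This is true only of the first window. Predictors for the second window are taken at month 2, after two months of use.
- *That the model is circular, with adherence predicted by its own components.* The article does not say which measures or cut-off define the binary variable, so the overlap is inferred from the Aim section's wording. Using earlier usage to predict adherence in the next window is an ordinary lagged model.
- *That the coefficients cannot be estimated, or are confounded with period.* The pooled coefficient can be estimated from the second window. Confounding with period would arise only if time were left out, and the text can be read as adding the predictors to the model that already contains time.

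One further objection is that the start of a window might mean its first days, since steps per day needs some interval. The counts would then not all be zero, but they would lie inside the window whose adherence they are meant to predict, which increases the possible overlap.

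**Conclusion.** The point stands in two parts.

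1. Aim 3 and its hypothesis make BDI-II change the outcome. Every adherence model described makes binary adherence the response, with largely the same usage measures as predictors, and no stated BDI-II model has a usage term. Followed as written, the plan does not test aim 3. This rests on the text alone and needs no numerical assumption.
2. In the predictor model, the month 0 to 2 window contributes no between-person information on workbooks, texts, videos and calls, which is up to 100 of 200 person-windows. This assumes 100 online participants and reads the start of the window as month 0. The consequence is that the coefficients rest on one window, not that they cannot be estimated.

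This should be corrected, but it is confined to a one-arm secondary aim. It does not touch the primary noninferiority comparison.

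**What to change.** Pre-specify a model for aim 3 in the online arm: regress 16-week BDI-II (or its change from baseline) on baseline BDI-II plus the continuous usage measures named in the Aim section (workbooks, texts, phone sessions, mean daily steps). Fix the exposure window in advance. Usage over weeks 0 to 8 is one defensible choice, because exposure then precedes outcome; usage over the full 16 weeks can be a sensitivity analysis, since the aim itself sets no early-use limit. If the SAP already contains such a model, the Hypothesis section should point to it in place of the GEE.

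Keep the GEE as a description of adherence over time. In its predictor model, use month 0 to 2 usage only to predict month 2 to 4 adherence, and state which measures make up the binary variable so that any overlap is visible.

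The cost is wording; the data are already to be collected. Two limits remain. The result is observational within one arm, so an association would not show that more use causes more improvement. Precision is also modest. Assuming a two-sided 5% test, 80% power and one usage measure correlated with the outcome, the detectable correlation by Fisher's z is tanh[(1.96 + 0.84)/√(n − 3)]. That is about 0.28 with 100 participants and 0.29 with 90, the latter matching the 10% online loss that the Missing Data section gives as an example.
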